## Measures Completed by All Participants

All patients will be asked to complete measures of symptoms, patient enablement, satisfaction, well-being, and quality of life as shown in Table 2.

We will explore the feasibility of two candidate primary outcomes that can apply to both OA consulters and others: symptom change, and symptom bothersomeness. The symptom change item asks patients to rate their overall symptoms now compared to two weeks ago, and was adapted from the COOP-WONCA charts. The symptom bothersomeness item asks patients to rate how bothersome their symptoms are, and was adapted from the item developed to assess severity of back pain in primary care. These are both single item generic measures, feasible to collect from a large number of patients with diverse health conditions. They add to the wellbeing and quality of life scales by specifically capturing patients' perceptions of symptoms.

The Patient Enablement Index (PEI) captures the extent to which patients feel confident and empowered by a consultation to cope with their illness, to keep healthy and to help themselves. The original publication described six items with 4 response options (much better/never/same or less/not applicable). Following other studies in the primary care and LifeGuide teams, we will modify the response scale to a 7-point agree-disagree Likert scale in order to increase sensitivity to change.

The Medical Interview Satisfaction Scale (MISS) measures patient satisfaction with the consultation and was used to detect post-intervention group differences in the Kepe Warm study. We have chosen the version of the MISS that has been specifically adapted and revalidated to be culturally appropriate for UK primary care. Patient satisfaction with the consultation is an important outcome for patients.

Patient wellbeing will be assessed using the Short Warwick Edinburgh Wellbeing Scale. The Warwick Edinburgh Wellbeing Scale underwent extensive development, focuses exclusively on positive aspects of wellbeing, and captures both hedonic and eudaimonic aspects of mental health. The short version is quicker to complete and retains robust psychometric properties as a unidimensional interval level scale.

For quality of life, we will use the SF-36

## Adverse Events Monitoring

All patients will be asked to complete an adverse events form at the follow-up measurement point. This form is adapted from the ACTIB trial and asks whether, since starting the study, participants have had any of the following events: a life threatening event, admission to hospital where you had to stay overnight, other medical events requiring medical attention. They are asked to provide

details of any such events. They are then asked “Has your health been adversely affected since the start of the study?” with Yes/No response options, and space for details if ‘Yes’. In line with the new OMERACT-OARSI core outcome domains for trials in hip and/or knee OA we will ask practices to notify us of the death of any patient participants during the patient-participation time period. Adverse events will be notified to relevant bodies, by the research team, as required.

### Process Measures

A series of process measures will be used to assess key variables from our draft logic model (see Figure 4) that we hypothesise mediate the relationship between undergoing EMPathicO training and improved patient outcomes.

**Figure 4. Draft Logic Model for EMPathicO**

[figure not shown]

## Directly Assessed

Intervention usage data from LifeGuide; this will tell us: when and for how long PCPs logged on to EMPathicO; which content was accessed (and for interactive components, engaged with) and for how long; the order in which content was accessed. Engaging with EMPathicO is an important component of our logic model. Collecting this data may suggest essential and non-essential parts of the intervention and will help us to understand engagement with EMPathicO, potentially informing further tweaks to the intervention before final full trial.

Films of 5 baseline consultations per PCP (at least 1 OA) and up to 9 consultations recorded at least 5 weeks after joining the study (post-intervention for the EMPathicO group). If all patient participants in the feasibility trial consent to having their consultation filmed (which we think is unlikely) then we could have a maximum of 280 filmed consultations (100 baseline consultations and 180 post-5 week consultations).

## Practitioner Reported

Practitioners will be asked to complete newly developed self-report measures of self-efficacy, outcome expectancy, and intentions for conveying empathy and optimism in consultations. Bespoke items have been drafted for this study as it is important to assess these constructs in relation to the specific behaviours that we are targeting, i.e. conveying empathy and optimism, and existing scales do not do this. We have developed our items following recommendations from Bandura's work on outcome expectancies and self-efficacy, the Theory of Planned Behaviour on intentions, and the Health Action Process Approach on coping efficacy. For example, Bandura recommends items assessing self-efficacy should concern the performance of a well-specified behaviour and should assess respondent's belief in their ability to perform that behaviour in difficult or challenging circumstances. This idea overlaps with coping self-efficacy in the Health Action Process Approach. Bandura further advises that such circumstances or impediments should be identified from qualitative work with the target respondent group and that items should capture a range of circumstances to help avoid floor or ceiling effects. In developing our self-efficacy items we have therefore drawn on the findings from our interviews with PCPs conducted during the Empathica Development project.

## Patient Reported

Patient perceptions of PCP clinical empathy will be assessed using the 10-item CARE. This is a validated, reliable, questionnaire that has been used extensively in UK primary care settings to assess patient perceptions of GP clinical empathy. EMPathicO aims to improve PCPs' communication of clinical empathy, and we expect that any such changes, to be clinically meaningful, should be noticed by patients. Patients' perceptions of clinical empathy are therefore an important component of the logic model.

Patient perceptions of PCP response expectancies will be assessed using a bespoke single item drafted for this study (as we could find no existing measure of this construct). EMPathicO aims to encourage PCPs to communicate positive but realistic expectations about the effectiveness of recommended or prescribed medications, management plans, therapies, referrals, etc. Therefore, we expect that patients in the intervention group should be able to perceive their PCP holding generally positive expectations as to the effectiveness of their treatment.

The Credibility Expectancy Questionnaire (CEQ) will be used to assess patient response expectancies and perceptions of treatment credibility. The expectancy subscale assesses the extent

to which patients believe their symptoms will improve. The credibility subscale assesses the extent to which patients believe their treatment to be credible in general for their condition. The CEQ is reliable and valid and has been used across many diverse settings and patient populations, including OA and primary care.

We will also assess patient response expectancies with a recently developed questionnaire specifically designed to assess patient expectations with respect to the outcome of medical treatments, the Treatment Expectation Questionnaire (TEX-Q) (unpublished data, [name], [name], [name], [name], [name] & [name], University Medical Center Hamburg-Eppendorf, Germany). This questionnaire is a better fit than the CEQ which instead seems to capture more general outcome expectancies that are not closely linked to a particular treatment. However, the TEX-Q is only now being validated in English and so we do not wish to rely on it alone as our only measure of response expectancies. By including both the CEQ and TEX-Q in this study we plan to provide additional validation data that we can process with advice from the TEX-Q team with whom we are collaborating.

### Recruitment Outcomes

PCP recruitment rates, i.e., number of practices and individual PCPs recruited per week as a function of number invited.

PCP intervention usage rates, i.e., number and proportion of consented PCPs logging on to the study website on LifeGuide.

Patient recruitment rates, i.e., number of all-consulters and OA patients recruited per PCP per recruitment session/day/week. We would also like to collect from practice admin the number of patients seen per PCP per recruitment session.

PCP attrition rates, i.e., number of practices and individual PCPs dropping out of the study and reasons given (if any).

Patient attrition rates, i.e., number and proportion of consented all-consulters and OA patients formally withdrawing from the study post-baseline or lost to follow-up, and reasons given (if any).

Feasibility of timing of outcome and process measures.

### Qualitative Data

We will invite participating PCPs and other practice staff who had a role in the trial to take part in a focus group (separate control/intervention) or a telephone interview. Participants will discuss the barriers/facilitators to implementing the trial and barriers/facilitators to accessing/ implementing EMPathicO. We may run more than one focus group for PCPs in each trial group, depending on participation rates, in order to minimise travel time for PCPs and ensure focus groups are of a suitable size to promote inclusive discussion (approximately 4-8 participants). We may need to interview some PCPs on the telephone if it proves prohibitively difficult to organise focus groups. If we do this, the focus group topic guide will be adapted slightly to ensure it is appropriate for an individual interview, but the topics discussed will remain the same. Initial analysis will begin shortly after commencing the focus groups/interviews, allowing data collection and analysis to proceed iteratively and to inform each other. We will stop interviewing PCPs and staff when we have spoken to a range of individuals and have generated sufficient data to address our research objectives.

We will invite a varied sample of patients to take part in a semi-structured telephone interview with a researcher. We will sample patients to ensure we speak with some patients: from each arm of the trial; from different primary care practices; who were recruited using different methods; and who had different patterns of missing data. Interviews will explore patients' experiences of trial processes and measures including questionnaire relevance and burden. Initial analysis will begin shortly after commencing the interviews, allowing data collection and analysis to proceed iteratively and to inform each other. Compared to face to face interviews, telephone interviews reduce the need for time-consuming, polluting, and costly travel, and when interviewers are well-trained can still produce good quality, rich, data. We will stop interviewing patients when we have spoken to a range of individuals and have generated sufficient data to address our research objectives.

### Planned Analysis

Data will be downloaded from LifeGuide and Qualtrics, cleaned, and imported into SPSS/STATS for analysis.

Scale scores on all outcome and process measures as appropriate will be computed following published guidelines.

We will examine the psychometric properties of all bespoke items and the TEX-Q (previously validated in German but not English) before included them in analyses.

Trends and effect sizes on process measures and patient reported outcomes will be examined.

Recruitment rates, attrition rates, and intervention usage data from LifeGuide will be examined.

We will explore how to analyse the films of baseline and post-randomisation consultations. This will include an exploration of how to sample films for analysis; how to code them reliably for the presence of techniques trained in EMPathicO using a simple checklist to be devised when the intervention is finalised; and how to explore for indicative evidence of PCP behaviour change following intervention.

We will analyse qualitative data descriptively using content analysis, possible supplemented by thematic analysis if time allows. Qualitative data from PCPs and patients will be analysed to suggest improvements to EMPathicO and to explore potential mechanisms of action that may or may not be consistent with the logic model. Qualitative data from PCPs and practice staff and patients and researchers' field notes will be analysed to suggest improvements to trial procedures. Qualitative data from patients will be analysed to inform choice of process and outcome measures for the full trial. Multiple researchers will be involved in the qualitative analysis to guard against idiosyncratic or overly-selective coding. NVivo will be used to facilitate coding and ensure an audit trail of the analysis is maintained.

The full trial draft power calculation is conservatively based on systematic reviews suggesting a standardized effect size of 0.25 for optimising expectations; sample size calculations will be further refined by calculating completion rates, ICCs, and standard deviations here.

The intervention and full trial design will be finalised after considering both quantitative and qualitative findings.

Table 3 summarises the trial objectives and maps them to data collected and the planned analyses.

**Table 3. Summary of Objectives, Associated Data, and Planned Analyses**

| Objective                                                                                                                                                                  | Data Collected                                                                        | Planned Analysis             |
|----------------------------------------------------------------------------------------------------------------------------------------------------------------------------|---------------------------------------------------------------------------------------|------------------------------|
| 1) to establish methods to maximise recruitment and minimise attrition, in practices with a range of socio-demographics (barriers and enablers)                            |                                                                                       |                              |
| a. to assess recruitment rates associated with different methods of recruitment                                                                                            | Recruitment rates by recruitment method, practice characteristics, and trial arm      | Cross tabulation             |
| b. to assess retention rates                                                                                                                                               | Retention rates by recruitment method, practice characteristics, and trial arm        | Descriptive                  |
| c. to identify barriers to recruitment of practices, PCPs (primary care practitioner e.g. GP, physiotherapist, or practice nurse), and patients, and ways to overcome them | Qualitative interviews and focus groups with patients, PCPs, and practice staff       | Qualitative content analysis |
| d. to identify enablers of recruitment of practices, PCPs, and patients, and ways to harness them                                                                          | Qualitative interviews and focus groups with patients, PCPs, and practice staff       | Qualitative content analysis |
| e. to identify barriers to retention of practices, PCPs, and patients, and ways to overcome them                                                                           | Qualitative interviews and focus groups with patients, PCPs, and practice staff       | Qualitative content analysis |
| f. to identify enablers of retention of practices, PCPs, and patients, and ways to harness them                                                                            | Qualitative interviews and focus groups with patients, PCPs, and practice staff       | Qualitative content analysis |
| 2) to identify feasible randomisation and consent procedures and finalise inclusion/exclusion criteria                                                                     |                                                                                       |                              |
| a. to test the feasibility of cluster randomisation.                                                                                                                       | Researchers' field notes
Qualitative interviews / focus groups with practice staff | Descriptive                  |
| b. to test the feasibility of different ways of taking patient consent, as outlined below.                                                                                 | Researchers' field notes                                                              | Descriptive                  |

|                                                                                          |                                                                                                             |                                                                    |
|------------------------------------------------------------------------------------------|-------------------------------------------------------------------------------------------------------------|--------------------------------------------------------------------|
|                                                                                          | Qualitative interviews and focus groups with patients, PCPs, and practice staff                             |                                                                    |
| 3) to finalise outcome and process measures                                              |                                                                                                             |                                                                    |
| a. to test the practical and ethical feasibility of video-recording consultations        | Researchers' field notes
Qualitative interviews and focus groups with patients, PCPs, and practice staff | Descriptive                                                        |
| b. to explore the relevance, feasibility and acceptability of potential outcome measures | Qualitative interviews and focus groups with patients and PCPs                                              | Directed content analysis                                          |
| c. to explore the relevance, feasibility and acceptability of potential process measures | Qualitative interviews and focus groups with patients and PCPs                                              | Directed content analysis                                          |
| d. to explore options for outcome and process measures for OA consultations and others   | Qualitative interviews and focus groups with patients and PCPs.
Missing data/completion rates            | Directed content analysis.

Descriptive                      |
| e. to explore feasible methods of analysing filmed consultations                         | Filmed consultations                                                                                        | Coding for evidence of Empathico techniques; reliability analysis. |
| f. to establish likely effect sizes                                                      | Questionnaire data                                                                                          | Effect size analysis                                               |
| g. to explore data for indicative changes in outcome and process measures                | Questionnaire data                                                                                          | Descriptive/Process                                                |
| h. to explore effective engagement with EMPathicO                                        | LifeGuide intervention usage data                                                                           | Usage/Process                                                      |

## Project Management

Table 4 shows the study Gantt chart. We plan to stagger recruitment and data collection across GP practices, commencing patient recruitment from approximately 2 practices at any one time. Each practice will initially have up to 5 weeks to recruit their patients (for those recruiting over Easter; 4 weeks otherwise). Allowing time to monitor and adjust our methods accordingly, the overall patient recruitment period will last a minimum of 14 weeks.

We will continue to meet regularly (typically weekly) to ensure effective team-working on this complex project, with monthly trial management group meetings and regular reporting as requested to our independent Trial Steering Committee (TSC). An additional Data Monitoring Committee was

deemed not necessary by the research team and the TSC, as this is a low risk feasibility trial and we have a statistician on the TSC.

### Ongoing Monitoring and Success Criteria

We will consider a full trial feasible and apply for funding if: 1. We achieve 70% of intended recruitment (14 PCPs, 42 patients); if we achieve 50% recruitment we will modify methods; if we achieve under 50% we will investigate reasons to see whether it can be addressed in a full trial. AND 2. 70% of GPs log onto LifeGuide; if 50% log on we will modify our incentive and/or reminder plan. We will aim for 80% completion of patient reported outcomes and change procedures if below 70%. We will monitor progress against these criteria at weekly team progress meetings and monthly trial management groups.

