  - b. to explore the relevance, feasibility and acceptability of potential outcome measures
  - c. to explore the relevance, feasibility and acceptability of potential process measures
  - d. to explore options for outcome and process measures for all-consulters and OA consultations
  - e. to explore feasible methods of analysing filmed consultations
  - f. to establish likely effect sizes
  - g. to explore data for indicative changes in outcome and process measures
  - h. to explore effective engagement with EMPathicO

To achieve these aims, we will conduct a cluster-randomised feasibility trial in 10 primary care practices (20 practitioners, 80 patients with osteoarthritis, and up to 200 patients attending primary care for other conditions) in the Wessex area. Practices will be randomised (1:1) to our new digital training package or to usual care control. We will explore different ways of recruiting and consenting patients. Patients will complete patient-reported outcome and process measures. Practitioners will complete additional process measures. We will collect extensive data on

intervention usage, recruitment and retention rates, and will explore the recording and analysis of consultations. We will conduct semi-structured qualitative telephone interviews with practitioners, practice staff, and patients. The data will be analysed and interpreted to further improve the intervention, refine our planned trial design including procedures, outcome measures, and sample size. We will consider a full trial feasible and apply for funding if: we achieve 70% of our intended recruitment (14 PCPs, 42 OA patients); if we achieve 50% recruitment we will modify methods; if we achieve under 50% we will investigate reasons to see whether it can be addressed in a full trial. AND 2. 70% of recruited GPs log onto the EMPathicO intervention on LifeGuide; if 50% log on we will modify our incentive and/or reminder plan during the feasibility study.

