## Methods

### Design

Mixed methods feasibility trial in primary care, designed to evaluate methods for a cluster-randomised trial of EMPathicO in all-consulters with a pre-planned sub-sample of patients with hip and/or knee OA. Henceforth, the participants who are not consulting with hip and/or knee OA are referred to as 'others'. The activities to be undertaken by practices and practitioners, and patients, are summarised in Figure 1 and Figure 2 respectively. The timings are subject to change during the feasibility trial depending on recruitment rates: for example, if necessary, we will extend the time available for recruiting patients.

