### Practitioners

Up to 20 consenting PCPs.

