### Patients

For randomisation: Up to 60 patients (3 per PCP) with clinically-diagnosed hip and/or knee OA who are seeking care for OA; and up to 120 other patients. An additional 100 patients (20 with OA) will be recruited for baseline video-recordings of consultations; these patients will not complete any questionnaires or interviews. Anecdotally we expect that for every 1 adult patient consulting for hip/knee OA there will be approximately 18 adult patients consulting for other conditions. However, we have decided to put an upper limit on the number of others to be recruited to this feasibility trial because:

1. Our main focus during intervention development and trial design has been hip/knee OA and we anticipate showing a larger effect in this more narrowly defined subgroup where pain is a primary complaint.
2. While we anticipate needing a larger sample to detect an effect in the more heterogeneous group of others, we do not anticipate needing a sample that is 18 times larger than the OA subgroup, which may be what we achieve if we simply invite all patients attending a participating PCP until we have 3 patients with OA (based on anecdotal evidence of approximate numbers of OA consultations per surgery). Such over-recruitment would be an unnecessary burden on patients' time and on our limited resources.
3. These numbers will provide enough information in the feasibility trial to be confident in our methods of recruiting these different groups and to estimate the variance in the primary outcome measure to inform power calculations for the planned definitive trial.

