#### *Alternative Approaches*

If our preferred approach is not working as well as we would like (see progression criteria below), then we would like to try the following opportunistic approaches (1 to 3) and advanced mail out approaches (4-5) to recruiting patients to participate in the trial:

- 1) PCP to inform, invite, take verbal and written consent, and collect baseline questionnaire at the start of the consultation.
- 2) PCP to inform, invite, take verbal consent, and collect baseline questionnaire at the start of the consultation. Research nurse/researcher to take written consent post-consultation.
- 3) Research nurse/researcher in reception/ waiting room to inform, invite, take verbal and written consent, and collect post-consultation outcomes, immediately post-consultation. NB This approach means no pre-consultation baseline data will be collected and that the consultation will not be filmed.
- 4) Invitation packs to be sent approximately one week in advance to patients with pre-booked appointments with a participating PCP. To include cover letter, PIS and written consent.
- 5) Database search and mailed invitations to patients to book an appointment with a participating PCP. To include cover letter, PIS and written consent. While this would represent a significant departure from usual practice, we would like to trial this approach if other approaches are proving ineffective.
- 6) Patient participants will be recruited through social media/patient organisations/snowball sampling. Patients who have planned/have had a recent telephone consultation with their PCP will give consent online and complete pre (if possible) and post consultation questionnaires.

We may also want to try the following different ways of collecting post-consultation questionnaires, if we need to adjust our preferred approach:

- 7) Post-consultation questionnaires to be included in initial approach to patients.
- 8) PCP to hand out post-consultation questionnaires at the end of each consultation for patients to complete in the waiting room and hand back at the practice in a sealed envelope or to take home and post back to the research team.

- 9) Research team to email post-consultation questionnaires on the same day as the consultation, requesting completion within 3 days.

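### The 70% recruitment go threshold is a head count with no time base, while recruiting time may be extended when recruitment is slow, so the band reached depends on how long practices stay open

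*Protocol*

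**What the plan says.** The go rule stands in the Protocol under Ongoing Monitoring and Success Criteria: a full trial counts as feasible if "We achieve 70% of intended recruitment (14 PCPs, 42 patients". The Expert Summary gives the same rule with the patient group named: "we achieve 70% of our intended recruitment (14 PCPs, 42 OA patients". Two lower bands follow. At 50% the team modifies its methods. Below 50% it looks into the reasons and asks whether a full trial could address them. No band has a date, a window or a rate attached.

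The denominators come from the Sample Size section: "Up to 20 consenting PCPs" and "Up to 60 patients (3 per PCP) with clinically-diagnosed hip and/or knee OA".

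The time allowed for recruitment is open-ended in the text. Under Design, timings may change with recruitment rates, and "if necessary, we will extend the time available for recruiting patients". Under Project Management, "Each practice will initially have up to 5 weeks to recruit their patients" applies to practices recruiting over Easter and 4 weeks to the others, in both cases as a starting allowance. The overall period is given as a minimum of 14 weeks, with no maximum.

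Under Recruitment Outcomes, the number of OA patients recruited per PCP is to be recorded by session, day or week. The go rule does not use it.

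**The concern.** Aim 1 of the trial is to find recruitment methods that work and to measure their rates. A progression rule on recruitment should therefore separate adequate from inadequate pace. A fixed total does this only if the time over which it accrues is also fixed. Here slow recruitment is the stated reason for allowing more time, so the shortfall that the rule should detect can be removed by waiting. Followed as written, the rule can call a full trial feasible on recruitment that would have fallen in the modify band, or below it, at the end of the initial windows.

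The rule also gives equal weight to every recruitment route. Under Alternative Approaches, option 5 mails patients an invitation to book an appointment, which the Protocol itself describes as far from usual practice. Patients found that way would count towards the 42 like any others.

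**Working it through.** **Inputs.** 20 PCPs and 60 OA patients, 3 per PCP (Sample Size). Initial window of 4 weeks, or 5 over Easter (Project Management). Bands at 70% and 50% (Ongoing Monitoring and Success Criteria). I read the modify band as 50% to below 70%, and I assume that all 20 PCPs take part and recruit at a constant pace.

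**The plan's own figures.** 0.70 × 20 = 14 PCPs and 0.70 × 60 = 42 OA patients. Both reproduce exactly. The 50% line is 0.50 × 60 = 30 OA patients.

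**Implied pace.** 60 / (20 × 4) = 0.75 OA patients per PCP-week. The Protocol does not state this rate; it follows from 3 per PCP in a 4-week window.

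**Band at 4 weeks, and time to reach 42.** With recruitment at a fraction f of the implied pace, the count at 4 weeks is 60f, and the time to reach 42 is 42 / (20 × 0.75 × f) = 2.8 / f weeks per practice.

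| f | Patients at 4 weeks | Band at 4 weeks | Weeks per practice to reach 42 | Band then |
|---|---|---|---|---|
| 1.00 | 60 | go | 2.8 | go |
| 0.70 | 42 | go | 4.0 | go |
| 0.50 | 30 | modify | 5.6 | go |
| 0.35 | 21 | under 50% | 8.0 | go |
| 0.25 | 15 | under 50% | 11.2 | go |

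**Sensitivity to the window.** If every practice had 5 weeks, the implied pace would be 60 / (20 × 5) = 0.60 per PCP-week and the time to 42 would be 42 / (20 × 0.60 × f) = 3.5 / f weeks. That is 7.0, 10.0 and 14.0 weeks for f = 0.50, 0.35 and 0.25. The figures move, but the pattern does not.

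**The bands as rates.**
- 4-week window: go at 42 / (20 × 4) = 0.525 per PCP-week; modify from 30 / (20 × 4) = 0.375.
- 5-week window: go at 42 / (20 × 5) = 0.42; modify from 30 / (20 × 5) = 0.30.

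**Rate and count differ if fewer PCPs join.** With 14 PCPs, a rate of 0.525 over 4 weeks gives 14 × 4 × 0.525 = 29.4 patients, whereas 42 patients in 4 weeks would need 42 / (14 × 4) = 0.75 per PCP-week, the full implied pace. The wording has to say which is meant.

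**The case against.** The strongest reply is that the rate is handled elsewhere. It is recorded under Recruitment Outcomes, Table 3 cross-tabulates recruitment by method, practice characteristics and arm, and Planned Analysis says that the full-trial design will be settled after weighing all the findings. A slow pace would be visible and could be used in planning. That is true, and it limits the harm. But the stated condition for applying for funding is the count, and nothing obliges the team to look at the pace when judging whether the condition is met.

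A second reply is that 0.75 per PCP-week is not the Protocol's figure. This also stands. It is a yardstick built from the targets and the initial windows, and the weeks quoted depend on it. That the band shifts with the time allowed does not.

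Two stronger readings are tempting, and the documents do not support them.

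- A reader might infer that the threshold can be met at any recruitment rate. Arithmetically any rate above zero gets there, but under Timing and Modality the Protocol says that time is limited by current funding, and the Gantt chart in Table 4 is not visible and may carry an end date. One can say only that the visible text sets no ceiling and that the criterion itself contains none.
- A reader might infer that on-plan recruitment would look like failure at the weekly meetings and set off a change of method, since "We will monitor progress against these criteria at weekly team progress meetings" and the alternative approaches are introduced with "If our preferred approach is not working as well as we would like (see progression criteria below". With about two practices starting at a time and 2 PCPs each, full recruitment gives 12/60 = 20% after the first pair and 24/60 = 40% after the second. Both fall under 50%, where the action is to look into reasons with a full trial in mind, not to switch methods. The third pair would bring 36/60 = 60%, inside the modify band, but nothing says that a running total is to be set against the final target. The trigger for alternative approaches is a matter of judgement, and a team that staggers its practices would naturally compare with what is due so far. What remains is a small gap in wording.

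**Conclusion.** The point holds for the final decision rule. The 70% threshold is a total without a time base, in a plan that lengthens recruitment when recruitment is slow. At half the implied pace the same practices are in the modify band at 4 weeks (30 patients) and in the go band at 5.6 weeks (42 patients). At 35% and 25% of that pace they start below 50% and reach go at 8.0 and 11.2 weeks. These figures assume 20 PCPs, constant accrual and the derived 0.75 per PCP-week.

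Because the rule governs an application for funding and the repair is only wording, it is worth correcting. The weekly monitoring question is a minor clarification, not a defect of the same kind.

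**What to change.** In both Ongoing Monitoring and Success Criteria and the Expert Summary, give the patient bands a time base. Either of two forms would do:

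1. OA patients per PCP-week open, counting extension weeks in the denominator: go at 0.525 or more and modify from 0.375 to below 0.525 for practices with a 4-week window; 0.42 and 0.30 for those with a 5-week window.
2. The count reached within each practice's initial window, against 3 OA patients per participating PCP.

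Keep the 14-PCP condition as a separate requirement, and say whether the patient rate replaces the total of 42 or is required in addition.

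Report patients recruited during extensions, and those who came through mailed invitations to book, separately alongside the rate. They need not be discarded: the trial is meant to adjust its methods as it runs. Nor should the threshold be restricted to routes intended for the full trial, because choosing those routes is one of this trial's objectives.

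As a minor clarification, state that weekly progress is judged pro rata to the PCPs opened to date.

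The cost is wording in two places plus that clarification. The recruitment data are already planned under Recruitment Outcomes. The drawback is that a slow site which eventually meets its count no longer contributes fully to a go decision.
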